**Methods/Design:**

The study, running in three European hospitals, is a multicenter, prospective, longitudinal, observational cohort study funded from the European Community's Seventh Framework Programme [FP7/2007-2013] within the project 'Impact of Specific Antibiotic Therapies on the prevalence of hUman host ResistaNt bacteria' (acronym SATURN). Nasal and rectal screening for methicillin-resistant *Staphylococcus aureus *and extended spectrum beta-lactamase-producing *Enterobacteriaceae *will be obtained at hospital admission, discharge, at antibiotic start (t_0_, within one hour) and at the following intervals: day 3 (t_1_), 7 (t_2_), 15 (t_3_), and 30 (t_4_). Two nested case-control studies will be performed. The objective of the first study will be to define individual level of risk related to specific antibiotics. Patients acquiring methicillin-resistant *Staphylococcus aureus *and extended spectrum beta-lactamase-producing *Enterobacteriaceae *(cases) will be compared with patients not acquiring antibiotic-resistant strains after starting antibiotic therapy (controls; ratio 1:4). To define the impact of antibiotics on new acquisition of target antibiotic-resistant bacteria, a second nested case-control study will be done (ratio 1:4). Control group will be selected among patients not receiving antibiotics, admitted in the same ward on the day of the corresponding case, with negative cultures at admission. Epidemiological, clinical and microbiological data will be prospective collected.

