## Testing the hypothesis

All adult patients (> 18 years) starting intravenous and/or oral antibiotic treatments during hospitalisation will be included in the study. Written informed consent will be obtained by every patient before study inclusion. Exclusion criteria will be pregnancy and recent nose surgery. Patients starting antibiotic therapy *per os *and/or intravenously will be sampled at antibiotic start (t_0_, within one hour) and at the following intervals: day 3 (t_1_), 7 (t_2_), 15 (t_3_), 30 (t_4_) (Figure 1). Patients colonised with MRSA and/or extended-spectrum β-lactamase (ESBL)-producing gram-negative bacteria before starting antibiotic therapy (t_0 _sample) will be excluded from follow-up cultures and analysis. Patients will be followed during the hospitalisation and afterwards for a total of 30-day from the inclusion in the study. Screening will be performed in outpatient clinics after patients' discharge from the hospital, if possible.

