### Statistical analysis

The assessable population for each target organism will include all treated patients from whom baseline screening and at least one follow-up screening will be available. The incidence of colonisation will be defined by the number of new cases of colonisation for 1,000 days of antibiotic therapy. Only patients with a negative baseline (t_0_) will be included in the longitudinal analysis. The length of exposure to antibiotic therapy for patients newly colonised by ARB will be defined by the number of days between the inclusion in the study and the date of the first positive sample. The length of exposure to antibiotic therapy for patients not colonised will be defined by the number of days between the inclusion in the study and the date of antibiotic discontinuation. The colonisation pressure will be calculated for each center and defined as the average point of prevalence for antibiotic-resistant bacteria for all days until acquisition or discharge. Time-to-event analysis (in days) between the inclusion in the study and the acquisition of colonisation will be done using Kaplan-Meier curves and Cox proportional hazard regression modeling in which the number of days until acquisition will be the dependent variable. Two nested case-control studies will be performed:

#### Case control study 1

To define the impact of antibiotics on new acquisition of MRSA and ESBL-producing *Enterobacteriaceae*, a matched case-control study will be done (ratio 1:4). The control group will be selected among patients not receiving antibiotics, admitted in the same ward on the day of the corresponding case, with negative cultures at hospital admission. Matching criteria will include: age (± 5 years), sex, and total length of hospitalisation.

#### Case control study 2

To define individual level of risk related to specific antibiotics, patients acquiring MRSA and ESBL-producing *Enterobacteriaceae *will be compared with patients not acquiring ARB after starting antibiotic therapy (ratio 1:4). Previously known risk factors or clinically relevant significant variables from the univariate analysis will be considered for inclusion in multivariate logistic regression analysis. The Hosmer and Lemeshow goodness-of-fit test will be used to assess model fit.

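### Case-control study 1 selects its controls by absence of antibiotics, so it cannot estimate the antibiotic effect it is meant to define

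*Protocol article*

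**What the plan says.** The aim of case-control study 1 (Statistical analysis) opens: "To define the impact of antibiotics on new acquisition of MRSA and ESBL-producing". Antibiotic treatment is therefore the exposure and acquisition the outcome.

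- **Controls.** The same paragraph reads: "The control group will be selected among patients not receiving antibiotics, admitted in the same ward on the day of the corresponding case". They must also be culture-negative at admission, and are matched on age, sex and total length of stay, four per case. The abstract, which lists this study second, repeats the rule: "Control group will be selected among patients not receiving antibiotics".
- **Cases.** No case definition is given under study 1. The source population is described elsewhere. Under Testing the hypothesis: "All adult patients (> 18 years) starting intravenous and/or oral antibiotic treatments during hospitalisation will be included in the study". Under Statistical analysis: "The assessable population for each target organism will include all treated patients from whom baseline screening" and at least one follow-up screening are available. The two studies are introduced with "Two nested case-control studies will be performed". Under Sample size, the 257 MRSA and 443 ESBL acquirers are to come from 8,565 patients who start antibiotics.
- **Swabs.** The abstract says that screening samples "will be obtained at hospital admission, discharge, at antibiotic start", and then on days 3, 7, 15 and 30.

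**The concern.** A case-control study estimates an exposure effect by comparing the odds of exposure in cases and controls. This works only if controls are sampled without regard to exposure, so that they show how common it is in the population that produced the cases. Here the rule sets exposure among controls to zero before any data are seen, and the entry rule sets it to 100% among the cases.

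Study 1 is the only planned comparison of antibiotics with no antibiotics, since study 2 contains treated patients only. The article expects the results to influence prescribing policy. A contrast produced entirely by selection could be taken for evidence of harm, or the stated question could simply go unanswered.

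**Working it through.** **Inputs.** 257 MRSA cases, 443 ESBL cases, 8,565 antibiotic starters, and acquisition of 3% (MRSA) and 5% (ESBL), all from Sample size. The 1:4 ratio is from case-control study 1.

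**The plan's own figures.** 257 / 0.03 = 8,567, against 8,565 stated, which agrees to rounding. Centre totals add up: 48 + 121 + 88 = 257 and 95 + 201 + 147 = 443. For ESBL, 0.05 × 8,565 = 428, not 443. That is a separate matter and does not affect this point. The agreement for MRSA supports reading the cases as acquirers among treated patients.

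**Controls.** 4 × 257 = 1,028 for MRSA; 4 × 443 = 1,772 for ESBL.

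**Tables forced by the selection rules:**

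| | Exposed | Unexposed |
|---|---|---|
| MRSA cases | 257 | 0 |
| MRSA controls | 0 | 1,028 |
| ESBL cases | 443 | 0 |
| ESBL controls | 0 | 1,772 |

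**Unmatched odds ratio.** For MRSA, (257 × 1,028) / (0 × 0) has no finite value. Adding 0.5 to each cell gives (257.5 × 1,028.5) / (0.5 × 0.5) = 1,059,355, a number set by the sample size alone.

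**Matched analysis.** Every set has one exposed case and four unexposed controls, so with log odds ratio β each set contributes e^β / (e^β + 4). This rises towards 1 as β grows, so the conditional likelihood has no finite maximum. Matching on age, sex and length of stay cannot restore variation in exposure.

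**Dependence on the truth.** Simulating the design with a true odds ratio of 0.5, 1.0 or 1.8 gave the same MRSA table (257, 0, 0, 1,028) each time. The data cannot separate protection, no effect and harm.

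**Dependence on the inferred case definition.** Suppose untreated acquirers were also taken as cases. Exposed controls remain zero. A set with an untreated case then has five unexposed members and contributes a constant 1/5, so the estimate still has no finite value.

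**With controls drawn regardless of exposure.** With all acquirers as cases, the simulated odds ratio was 1.00 to 1.02 for a true 1.0, 1.78 to 1.86 for 1.8, and 0.51 for 0.5 (30% or 50% of ward patients exposed, assumed). For a true odds ratio of 1.8 and two-sided 0.05, unmatched power was 0.96 to 0.99 with 257 cases and 1,028 controls, and above 0.99 with 443 and 1,772. This assumes 20% to 60% antibiotic use among controls, which the article does not give. It also assumes the full case numbers and equal detection, so it is an upper guide.

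**The case against.** The strongest reply is that study 1 is a loosely labelled matched comparison of treated with untreated patients, with acquisition as the outcome. This would explain why controls need be negative only at admission (at risk, not outcome-free), why matching is on total stay (similar time at risk), and why a discharge swab is listed. On that reading the effect could be estimated. But the article calls the study nested and case-control, and ties each control to a corresponding case. If every enrolled patient were a case, a 1:4 ratio would need 4 × 8,565 = 34,260 untreated patients, and none are planned. The reading does not fit the text.

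Antibiotic therapy in the previous 30 days is a listed variable and may vary among controls. It is prior therapy, not the treatment whose effect is in question.

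Some of the reply stands. The case group is inferred, not stated. No model is named for study 1, and the article condenses a fuller protocol. The control rule, however, is stated twice, so this is not missing detail.

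Three stronger readings are tempting and unsupported:
- *The main result is undermined.* The primary outcome (acquisitions per 1,000 antibiotic-days), the Cox model and study 2 all use the treated cohort and do not draw on these controls.
- *Cases have four more chances of detection.* Four is a maximum. Screening after discharge is done only if possible, and swabs after the first positive are irrelevant. The schedule for untreated patients is not shown.
- *Controls are known to be outcome-free, or known not to be.* Negative admission cultures show neither, so an undetected acquirer may serve as a control, but how often cannot be derived.

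**Conclusion.** As written, study 1 cannot meet its stated aim. The control rule fixes exposure at zero in controls. With treated acquirers as cases, the counts are forced to 257/0 against 0/1,028 (MRSA) and 443/0 against 0/1,772 (ESBL). The antibiotic odds ratio has no finite estimate and is uninformative under any true effect. More patients or covariate adjustment would not help. Other risk factors, such as catheters or transfers, could still be compared, but those contrasts would mix acquiring the organism with being treated.

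The exact case counts rest on the inferred case definition and the planned numbers. The lack of a finite estimate does not, provided study 1 is the case-control study of acquisition that the article says it is. The fault is confined to this one nested analysis.

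**What to change.** **Control rule.** Select controls by outcome and not by exposure: patients of the same ward, negative at admission and with no positive swab up to a comparable length of stay, whether or not they received antibiotics.

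**Cases.** State the definition. Include untreated acquirers found on the admission and discharge swabs alongside treated ones.

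**Analysis.** Compare prior antibiotic exposure by conditional logistic regression, separately for each organism.

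**Detection.** For this analysis only, base acquisition status on the swabs common to both groups (admission and discharge). Otherwise treated patients, with interim swabs, have more opportunity to be found positive.

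**Cost.** More than wording. Cohort entry covers only antibiotic starters and recruitment is under way, so untreated acquirers would need to be identified, consented and documented. Using only the common swabs leaves fewer usable cases, so power will be below the figures above. A discharge swab also cannot date the acquisition, and being negative on a given day during the stay cannot be verified in a patient swabbed only at admission and discharge.

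**If untreated patients have no discharge swab,** withdraw the statement that study 1 defines the effect of antibiotics, and present it as a descriptive comparison of treated acquirers with untreated patients. Comparing time on and off antibiotics within the cohort is no substitute: every member is treated, so there is no never-treated time.

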## Presentation of the hypothesis

We designed a 2-year observational cohort study (WorkPackage 4 of the EU-funded SATURN project) in order to clarify and determine the role of antibiotic therapy in the acquisition of ARB in hospitalized patients. The study will run in three European hospitals, ranging from 700 to 3,500-bed capacity: Università Cattolica Sacro Cuore "Policlinico A. Gemelli" (UCSC, Rome, Italy), Institute of Infectious Diseases "Matei Bals" (IDMB, Bucharest, Romania), and Clinical Center of Serbia (CCS, Belgrade, Serbia). Overall, 6 medical and 6 surgical wards will be included. All centers obtained ethical approval from the local institution review board.

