### Sample size

Since the rate of acquisition of ESBL-producing gram-negative bacteria in patients receiving antibiotic therapy has not been established in prospective cohort studies, prevalence proportion was derived from retrospective case-control studies and defined as 5%. Sample size calculation for the rate of new acquisition of MRSA has been derived by a previous study where the acquisition rate, after starting antibiotic therapy, was 3% [4]. To be able to analyse 257 patients newly colonised by MRSA and 443 by ESBL-producing gram-negative, 8565 patients starting antibiotic therapy need to be enrolled. According to the number of hospital admission/year and percentage of patients starting antibiotic in each ward, the clinical centers are required to provide the following numbers of patients with new colonisation by MRSA/ESBL *Enterobacteriaceae*: 48/95, 121/201, and 88/147 for UCSC, IDMB, CCS, respectively.

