## Implications of the hypothesis

SATURN project is a European multicentre study that aims to provide an in-depth knowledge of ARB acquisition through the analysis of antibiotic classes, duration of treatment and dosage in the nosocomial setting by a multidisciplinary approach. The SATURN project website http://www.saturn-project.eu provides the information and details concerning the different WPs and the entire project.

Several outcomes will be obtained at the end of the study (December 2014, expected): the rate of acquisition of target ARB by 1,000 antibiotic-days according to different classes of antibiotics, duration of therapy, and antibiotic combinations (monotherapy versus combinations); risk factors associated with new colonisation by target ARB; and risks for nosocomial infections due to target ARB after a cycle of antibiotic therapy adjusted by length of hospitalisation and ward colonisation pressure.

The WP4 study is currently recruiting patients in all clinical centers. The accomplishment of the study will be pursued thanks to the great strive of all clinicians, nurses and microbiology staff in every study step. An advertising campaign (posters, stickers and pictures) was performed in the selected wards in order to thrill and sensitise the recruited staff.

The results of the study should lead to the design of specific infection control measures for preventing spread of ARB in hospitalised non-ICU patients undergoing antibiotic therapy. A potential benefit for selective screening in high-risk patients during antibiotic therapy or shorter duration of antibiotics in such patients might be hypothesised. Readily available colonisation information could impact empiric therapy for nosocomial infections or, for example, the potential need of mupirocin prophylaxis for patients colonised by MRSA during hospitalisation. Assessment of the usefulness of the recommendations derived from the results of the SATURN study should be of valuable help for those in charge of infection control, for hospital administrators, and for those managing budgets of large healthcare organisations.

We do expect that SATURN project results will have a direct impact on clinical practice, improving the appropriateness of antibiotic prescribing policy, the prevention of antibiotic-resistant infections and the heightener of patients' quality care.

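### Case control study 1 matches on total length of stay, which for in-hospital acquisitions includes days after the outcome; match on time at risk instead

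*Protocol article*

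**What the plan says.** The Statistical analysis section of the Protocol article describes two nested case-control studies. Case control study 1, which the Abstract lists second, asks what antibiotics do to new acquisition of MRSA and ESBL producers. It is to be "a matched case-control study will be done (ratio 1:4", four controls to a case. On the control group: "The control group will be selected among patients not receiving antibiotics", and these patients are to be "admitted in the same ward on the day of the corresponding case, with negative cultures at hospital admission". The matching rule follows: "Matching criteria will include: age (± 5 years), sex, and total length of hospitalisation".

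The cohort analysis in the same section handles time differently. There, a newly colonised patient's exposure runs from inclusion to the first positive sample and stops. Under Testing the hypothesis, follow-up lasts 30 days from inclusion and continues after discharge where possible.

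**The concern.** Total stay is known only at discharge. For a patient who acquires in hospital it has two parts: the days at risk before the first positive sample, and the days after it. The second part can be lengthened by infection with the acquired organism, which is the study's secondary outcome, and by the antibiotic course. A matching variable with that second part in it is partly downstream of both outcome and exposure.

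It also fails to equalise time at risk. Two patients with equal total stays do not have equal windows if one stopped being at risk part of the way through. Study 1 is the study's stated means of measuring the effect of antibiotics against no antibiotics, so the comparability of its controls matters.

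**Working it through.** **1. Which days are matched.** Let a case acquire on day *a* of a stay of *L* days.

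- Case's time at risk in hospital: *a* days.
- Control matched on total stay: about *L* days, none of them ended by acquisition.
- Ratio of windows: *L*/*a*, above 1 whenever *a* < *L*.

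As a purely hypothetical illustration, *a* = 7 and *L* = 20 give 20/7 = 2.9. The article gives neither quantity, so this is not an estimate for the study. If the first positive sample comes after discharge, the stay contains no post-acquisition days and the problem does not arise.

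**2. Which covariates are touched.** The Variables section records urinary catheters, central venous catheters, surgery and room sharing at each clinical follow-up; these can accumulate. If they are counted to acquisition in cases and to discharge in controls, controls have longer to collect them. If they are counted over the whole stay in both, the case's record includes events after the outcome. Items fixed at admission or in earlier history cannot grow with stay.

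**3. Supply of controls (conditional).** Inputs from the article:

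- Wards: "Overall, 6 medical and 6 surgical wards will be included", so 12.
- Duration: "We designed a 2-year observational cohort study", so 730 days.
- Cohort: "8565 patients starting antibiotic therapy need to be enrolled". Check against the stated MRSA count and rate: 257/0.03 = 8,567, which agrees with 8,565.
- Controls needed at 1:4: 4 × 257 = 1,028 for MRSA and 4 × 443 = 1,772 for ESBL, together 2,800 if no patient counts for both.

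Antibiotic starts per ward-day = 8,565/(12 × 730) = 0.98.

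The share *s* of admissions treated is not given; 20% to 60% is assumed. Untreated admissions per ward-day = 0.98 × (1 − *s*)/*s*:

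| *s* | untreated admissions per ward-day |
|---|---|
| 0.2 | 3.9 |
| 0.3 | 2.28 |
| 0.4 | 1.47 |
| 0.5 | 0.98 |
| 0.6 | 0.65 |

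Further assumptions: 0.5 share the case's sex, 0.15 to 0.25 fall within 5 years of age, and 0.2 to 0.4 have a similar stay.

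- *Admitted on that day, sex and age matched:* 0.65 × 0.5 × 0.15 = 0.05 to 3.9 × 0.5 × 0.25 = 0.49 per case. With a Poisson count, the chance of at least four is at most 0.2%.
- *Stay matched as well:* 0.05 × 0.2 = 0.01 to 0.49 × 0.4 = 0.20 per case, so 1% to 18% of cases have even one control.
- *Present in the ward on that day, assumed census 20 to 60:* 20 × 0.4 × 0.5 × 0.15 = 0.6 to 60 × 0.8 × 0.5 × 0.25 = 6.0 without stay; 0.6 × 0.2 = 0.12 to 6.0 × 0.4 = 2.4 with it, where the chance of at least four is at most 22%.

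**The case against.** Several objections stand and limit the point.

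- **The antibiotic odds ratio.** A reader might infer that longer control windows pull the antibiotic effect toward 1. The document does not support that: controls are untreated by selection, so extra days cannot add antibiotic exposure to them. The accumulation problem concerns the other covariates, and no direction can be given for bias in the antibiotic odds ratio.
- **Colonisation pressure.** It may look like another inflated exposure. The article defines it as an average prevalence, already cut off at acquisition, so it does not accumulate.
- **The Implications section.** It describes infection risk as "adjusted by length of hospitalisation and ward colonisation pressure", which might be read as the same error again. It may equally mean the denominator given under Outcomes, infections per 1,000 hospital days, so it is not counted here.
- **Infection is not universal.** The Background cites 9% of newly colonised patients developing infection in an earlier cohort. Lengthening of stay by that route would then affect a minority, although the unequal windows apply to every in-hospital acquisition followed by further days in hospital.
- **The supply figures rest on assumptions.** The article gives no ward census, admission count or treated share, and 8,565 is an enrolment target. The wording may also mean present in the ward rather than admitted that day. It would be too strong to say that four controls cannot be found.
- **Tolerance for stay and handling of unmatched cases** may be left to the full protocol; their absence from an article is not held against it.

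None of this defends total stay as the variable to match on.

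**Conclusion.** The matching variable should be changed. That conclusion follows from the text alone: for in-hospital acquisitions total stay contains post-outcome days, and it does not give case and control the same time at risk. The cohort analysis in the same section already stops at the first positive sample. The amount of bias cannot be calculated from the article, because the split of stay before and after acquisition is not stated.

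The shortage of controls is a conditional finding. If controls must be admitted on the given day, the expected number stays well below four across the assumed range, and doubling the pool raises the best sex- and age-matched case only to 2 × 0.49 = 0.98. If presence in the ward is enough, the expected number is still below four with stay matching (0.12 to 2.4), but may reach four in large wards without it (0.6 to 6.0).

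The primary acquisition rate and the Kaplan-Meier and Cox analyses do not use this matching and are unaffected.

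**What to change.** 1. Replace total stay with time at risk. Choose controls whose stay is at least as long as the case's days from admission to first positive sample, or to discharge if the case is first positive afterwards. Count control covariates only up to that same day of stay.
2. Define eligible controls as not known positive by that day, using the swabs already planned. Untreated patients are swabbed only at admission and discharge, so proof of negativity on the day itself would need new sampling. The cost is that a few controls may be unrecognised carriers.
3. State whether the ward rule means admitted or present on the day. If admitted, use the same ward within a calendar window. As a guide under the assumptions above, an expected four controls before the stay condition needs 4/0.49 = 8 to 4/0.05 = 80 days of ward admissions with sex and age matched, or 4/3.9 = 1 to 4/0.65 = 6 days with neither matched.
4. If supply is still short, drop age and sex as matching criteria and adjust for them in a conditional model.

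The change is to wording and to the control-selection procedure, with no extra swabs. The price is slightly looser calendar, age and sex matching. The Implications section says recruitment is under way, so it should be settled before controls are selected.

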## Background

Despite many efforts, the control of nosocomial antibiotic-resistant infections is still a permanent and unresolved issue in healthcare institutions worldwide facing increased morbidity, mortality and hospital costs [1-3]. Selective pressure exerted by antibiotics plays a central role on the acquisition, selection, persistence and transmission of resistant pathogens which may include the following effects: (1) eradication of the susceptible skin and gut flora will increase the likelihood of acquisition of antibiotic-resistant organisms, especially in settings with endemic resistance; (2) antibiotics select for pre-existing antibiotic-resistant bacteria (ARB) in carriers and enhance the likelihood of spread; (3) antibiotic selection pressure may transform low-level carriers to high-level spreaders; (4) antibiotics active against antibiotic-susceptible bacteria may convert carriers of susceptible bacteria to non-carriers, indirectly promoting acquisition and spread of ARB; (5) antibiotic exposure may increase the risk of endogenous infection with ARB related to changes in colonisation resistance and bacterial virulence at the individual host level [4]. Numerous papers demonstrated that prior antimicrobial drug exposure is a strong risk factor for colonisation and infection due to a drug resistant pathogen [5,6]. A meta-analysis that included 76 studies for a total of 24,230 patients documented that the risk of acquiring methicillin-resistant *Staphylococcus aureus *(MRSA) was increased by 1.8-fold in patients who had taken antibiotics. Antibiotic exposure was determined in the 126 days preceding MRSA isolation [7]. Such risk was almost 3-fold greater after using quinolones or glycopeptides and 2-fold for cephalosporins. A multicentre prospective cohort study conducted in several Italian hospitals showed that 5% of patients were newly colonised by ARB including MRSA in nasal samples, after starting antibiotic therapy. Nine percent of those patients developed an infection by the same strain over the 30-day follow-up. The use of carbapenems was associated with the highest incidence of colonisation with eight new cases of MRSA colonisation for 1,000 antibiotic-day [4].

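### Case-control study 2 can give only antibiotic-versus-antibiotic contrasts, and its variable rule lets the reference for those contrasts depend on the data

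*Protocol article*

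**What the plan says.** Enrolment is limited to antibiotic starters (Testing the hypothesis): "All adult patients (> 18 years) starting intravenous and/or oral antibiotic treatments during hospitalisation will be included in the study". The analysis set is limited in the same way (Statistical analysis): "The assessable population for each target organism will include all treated patients".

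Case control study 2 (listed first of the two in the Abstract) has the aim "To define individual level of risk related to specific antibiotics". Its design is that acquirers "will be compared with patients not acquiring ARB after starting antibiotic therapy (ratio 1:4". No reference drug or class is named. The rule for choosing model terms is: "Previously known risk factors or clinically relevant significant variables from the univariate analysis will be considered for inclusion in multivariate logistic regression analysis".

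Case control study 1 has the untreated comparison: "The control group will be selected among patients not receiving antibiotics". Its aim is the effect of antibiotics as a whole.

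The Background gives class-specific MRSA risks: "Such risk was almost 3-fold greater after using quinolones or glycopeptides and 2-fold for cephalosporins". The figure for any antibiotic is 1.8-fold. Outcomes and Implications of the hypothesis also plan acquisition rates per 1,000 antibiotic-days by class, and Outcomes adds single drugs.

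**The concern.** Two things do not fit together.

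First, the aim speaks of each drug's level of risk, but nobody in study 2 is untreated. A patient not exposed to a given class has taken another antibiotic. An odds ratio near 1 then means about as risky as the comparison antibiotics. A reader who takes the aim at its word may read it as no added risk.

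Second, the antibiotic terms are the exposures of interest, yet the rule treats them like any other candidate covariate. A class that is neither counted as a known risk factor nor significant on its own can be left out. Its users then become part of the reference for the classes that remain, so what the reported odds ratios compare depends on which terms passed the screen.

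The article expects the results to shape prescribing policy, so what each odds ratio is relative to matters.

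**Working it through.** **Plan's own figure.** 8,565 patients × 3% = 256.95, which reproduces the 257 MRSA cases in Sample size. At 1:4 this gives 4 × 257 = 1,028 controls.

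**Inputs from the article.** MRSA risk against no antibiotic: 1.8-fold for any antibiotic, 2-fold for cephalosporins, almost 3-fold for quinolones or glycopeptides (Background). Acquisition 3%; 257 cases (Sample size).

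**Assumptions.** The article gives no class shares, significance level or exposure coding. I take shares *p* of 5% to 40%, two-sided 5%, a yes/no term for the class in the univariate step, and no combination therapy. The article has no class-specific risks for ESBL, so only MRSA is sized.

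**Check 1: a 2-fold class within a 1.8-fold average.**
- Risk without antibiotics: r0 = 0.03/1.8 = 0.01667. Risk in the class: a = 2 × r0 = 0.03333.
- Mean relative risk of the other users: m = (1.8 − 2p)/(1 − p). Their risk: b = m × r0.
- Odds ratio among users = [a/(1 − a)]/[b/(1 − b)].
- Exposure in cases = p·a/0.03; in controls = p(1 − a)/0.97. Chance of significance: two-proportion normal approximation, both tails.

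Example, p = 20%: m = (1.8 − 0.4)/0.8 = 1.75; b = 0.02917; odds ratio = 0.03448/0.03004 = 1.15. Exposure is 22.2% in cases and 19.9% in controls, and the chance of significance is about 13%.

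| Share p | m | Odds ratio among users | Chance of significance |
|---|---|---|---|
| 5% | 1.79 | 1.12 | 7% |
| 10% | 1.78 | 1.13 | 9% |
| 20% | 1.75 | 1.15 | 13% |
| 30% | 1.71 | 1.17 | 19% |
| 40% | 1.67 | 1.21 | 27% |

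Against no antibiotic, the same class has an odds ratio of about 2.03: (0.03333/0.96667)/(0.01667/0.98333).

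**Check 2: a 3-fold class, same average.** With m = (1.8 − 3p)/(1 − p), the odds ratio runs from 1.77 (p = 5%) to 3.1 (p = 40%). The chance of significance is 56% at p = 5%, 85% at 10% and 99% or more from 20%.

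**Check 3: assumed class mixes.** Cephalosporins 25% or 50%, quinolones 15% or 30%, glycopeptides 5% or 10%, the remainder at relative risk 1.0 or 1.5; the average is not tied to 1.8. Cephalosporins against all other users:
- Lowest (50/30/10%, remainder 10% at 1.5): others average (0.30×3 + 0.10×3 + 0.10×1.5)/0.50 = 2.70; ratio 2/2.70 = 0.74.
- Highest (25/15/5%, remainder 55% at 1.0): others average (0.15×3 + 0.05×3 + 0.55×1.0)/0.75 = 1.53; ratio 2/1.53 = 1.30.

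**Check 4: what dropping a term does.** Take the 25/15/5/55% mix with the remainder at 1.5. With the remainder as reference, the quinolone ratio is 3/1.5 = 2.00. If a 2-fold class with a 25% share is dropped, the reference becomes (0.25×2 + 0.55×1.5)/0.80 = 1.66, and the quinolone ratio becomes 3/1.66 = 1.81. The data on quinolones are unchanged; only the reference has moved.

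**The case against.** The design is deliberate. Study 1 takes antibiotics against none and study 2 takes users against users. A comparison among users is valid and limits confounding by indication, and an odds ratio near 1 correctly says that a class is about average. The article never says it would be read as no added risk. All of this stands: the fault lies in how the aim is worded, not in the choice of controls.

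A reader might infer that study 2 is the only analysis of specific-antibiotic risk. It is not. Outcomes plans rates per 1,000 antibiotic-days by class and single drug, and these need no reference group. They have no untreated comparator, though, and the text describes no adjustment for them.

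A reader might also infer that a class which doubles risk will usually be screened out, because it rarely reaches significance. The rule does not support that. Known risk factors may enter without significance, and the Background itself names cephalosporins, quinolones and glycopeptides. The 7% to 27% is a chance of univariate significance, not of inclusion in the model. The screen bites on classes not already counted as known.

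Exposure coding and the reference category may well be set in an analysis plan that is not shown. The article does not say that each drug is tested against all others, so the absence of that detail is not held against it. The aim and the selection rule, however, are stated.

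**Conclusion.** The point holds as a cheap improvement, not as a flaw that invalidates study 2. Study 2 estimates contrasts between antibiotics, while its aim can be read as the risk of each drug in its own right. Its stated rule also allows the exposures of interest to be selected by p-value, which makes the reference data-dependent.

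On the Background's MRSA figures, a 2-fold class shows an odds ratio of about 1.12 to 1.21 among users and is significant in about 7% to 27% of studies of the planned size. Across the assumed mixes its ratio is about 0.74 to 1.30. A 3-fold class would usually still stand out, unless rarely used. These sizes rest on assumed class shares, a two-sided 5% level, yes/no coding and single-drug therapy, and on carrying the Background's relative risks over to this cohort.

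**What to change.** In case-control study 2:

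- Name one reference class, fixed before outcome data are seen.
- Fit all antibiotic classes jointly against it and keep them in the model whatever their univariate p-value. Leave the selection rule for the other covariates.
- Restate the aim and conclusions as contrasts between antibiotics.
- Present the odds ratios beside the planned class- and drug-specific rates per 1,000 antibiotic-days, so that a ratio near 1 is seen with the absolute rate behind it.

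Cost: wording and model specification only, with no new data or patients. A few more model terms are used, and the claim becomes openly relative. It does not supply a no-antibiotic comparison: a 2-fold class against a 2-fold reference class still gives a ratio of 1.0.
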